**Figure 2 fig2:**
[figure not shown]
Individualized and normative feedback regarding PA per week during the past 5 weeks **(A)** as well as portions of fruit and vegetable, and taels of meat, fish, egg, and alternatives consumption in average per day during the past 2 weeks **(B)** for the blended intervention group.

Each weekly web-based section for PA and diet will last about 15 minutes. In the first week, once the participants complete the face-to-face intervention, the researcher will immediately organize a web-based intervention course for older adults at the PA gymnasium and the senior center for diet, respectively. The researcher will first introduce the website’s content and then demonstrate the steps to use this web-based program. Afterward, research helpers will guide participants in accessing the website and finishing the online study. In the 2nd week, the web-based intervention course will be continuously offered at the gym and the senior center to ensure older adults are familiar with the website’s usage. From the 3rd week, participants will be encouraged to finish the online courses at home to support transfer.

#### Control group

2.3.3

The participants in the control group will receive a biweekly telephone call. Each call will last about 5 minutes. The participants will be asked several health-related questions, such as “Has your physical activity changed in the last 2 weeks?” “If it changed, what are the reasons for the increase or decrease?” “Have you changed your diet in the last 2 weeks?” and “What has changed? What are the reasons for the increase or decrease if it changed?”

### Outcome evaluation of the intervention

2.4

All the outcomes will be measured at T1 (baseline pre-test), T2 (post-test), and T3 (follow-up). Only demographics will be collected at T1. All measurement scales will be in Cantonese, which has been widely used in previous studies conducted in Hong Kong.

#### Primary outcomes: behavior indicators

2.4.1

##### Physical activity (PA)

2.4.1.1

The waist-worn accelerometer (wGT3XBT, ActiGraph Inc., Pensacola, FL, USA) will objectively assess moderate-to-vigorous intensity physical activity (MVPA) during the last 7 days. The participants will be guided to wear accelerometers attached to elastic belts around their waists during all waking hours for seven consecutive days. They must remove the waist-worn accelerometers only during sleeping or water-based activities (43). The Troiano wear time validation algorithm will be applied to activity counts (44). With this algorithm, periods of 60+ consecutive minutes of continuous zero counts with a tolerance of up to 2 minutes of activity counts between 0 to 100 counts/min will be classified as non-wear time (44). Data of at least 10 hours per day for at least 3 days will be considered valid and included in data analysis according to a previous systematic review (45). For the estimated PA intensity, the Sasaki et al. cut-point will be applied, 200–2,690 counts/min is for LPA, and ≥ 2,691 counts/min is for MVPA (46).

##### Fruit and vegetable intake (FVI) and meat, fish, egg & alternatives (MFEA)

2.4.1.2

To assess the FVI and MFEA during the past 7 days, participants will be asked to finish a diet record booklet and fill in how many portions of fruit, vegetable, and fruit and vegetable juice as well as how many taels of meat, fish, egg, and alternatives they have consumed within 1 day. The items will include “On the first day, I ate xxx portions of vegetables, I ate xxx portions of fruits, I drank xxx portions of vegetable and fruit juice. In total, xxx portions fruit and vegetables” and “On the first day, I ate xxx taels of meat (including fish), I ate xxx taels of eggs, I ate xxx taels of alternatives and a total of xxx taels meat, fish, egg, and alternatives.” The average number of FVI and MFEA they ate daily will be calculated based on the records they filled out during the past 7 days. These items are developed based on the diet recommendations provided by the Center for Health Protection Department of Health in Hong Kong (47). One tael is equal to 37.799 grams. Each participant will receive an assessment guide booklet on the portion of fruit and vegetables and the tael of MFEA.

#### Secondary outcomes: health outcomes

2.4.2

##### Physical health outcomes

2.4.2.1

The Senior Fitness Test (SFT) Manual will be applied to assess the physical fitness of participants (48). The testing materials have been widely used in many countries and translated into many languages, including Chinese (49). The physical fitness testing includes the measurements of the 30-Second Chair Stand Test (lower body strength), 30-Second Arm Curl Test (upper body strength), 2-Minute Step Test (aerobic endurance), Chair Sit-and-Reach Test (lower body flexibility), Back Scratch Test (upper body flexibility), 8-foot Up-and-Go Test (agility and dynamic balance), and body mass index (BMI). Detailed testing guidance will be provided during testing. For example, 30-Second Chair Stand Test will be used to test lower body strength. Required measuring tools include a straight back or folding chair without armrests (seat 17 inches/43 cm high) and a stopwatch. The participant will be asked to sit in the middle of the seat, with their feet shoulder-width apart, flat on the floor. The arms should be crossed at the wrists and held close to the chest. The participant will be required to keep their back straight and keep their arms against the chest. After listening to the “Go” instruction, the participant should rise to a full standing position, and then sit back down again. The participant should repeat this action for 30 s. If the participant has completed a full stand from the sitting position when the time has elapsed, the final stand is counted in the total. The reliability of SFT items ranged from 0.80 to 0.98 (49).

The blood pressure will be measured by an automated portable device (Omron HEM-7121 Standard, Japan) following the procedure guidelines (50). Participants will be asked to sit quietly for 5–10 minutes before their blood pressure is measured. The blood pressure will then be recorded on an electronic screen and written on paper for recording. The unit would be mmHg. Capillary blood samples will be collected by finger-prick (51). The glycosylated hemoglobin (HbA1c, mmol/mol) and lipid (Total Cholesterol, CHOL; triglycerides, TG; high-density lipoprotein, HDL; mg/dL) will be tested by Point of Care (POC) Cobas b 101 system (Roche Diagnostics, Mannheim, Germany). A 30 uL fingertip blood sample will be collected from participants and immediately tested using two test trips. The system can generate HbA1c and lipid assay results by using 2 uL for the HbA1c test and 19 uL for the lipid test by finger-prick blood samples within 15 minutes (52). Participants will be asked to stay in a fasted state for 12 hours before the blood test.

##### Mental health outcomes

2.4.2.2

The Geriatric Depression Scale 15-item (GDS-15) - Cantonese Version will be used to assess depression among participants. The validity and reliability of the GDS-15 were validated as satisfactory among Chinese older adults in previous studies and were regarded as a valuable method for measuring depression in older adults (Cronbach’s *α* = 0.81–0.83) (53, 54). Participants will be asked 15 items referring to the past week, such as “Are you satisfied with your life?” and “Have you dropped many of your activities and interests?.” Answers are indicated as yes “1” or no “0.” For items 1, 5, 7, 11, and 13, the answer is yes “0” or no “1.”

The Chinese translation of the 6-item De Jong Gierveld Loneliness Scale will be applied to assessing loneliness. This scale was reliable and valid for measuring loneliness among Hong Kong older adults (Cronbach *α* = 0.76) (55). The participants will be informed, “Please see if these statements describe your situations or feelings now. If you think that they are describing you, answer yes; if you disagree with the statements, answer more or less; if you do not think that they are describing you, answer no.” Participants will be asked six items including two domains (emotional loneliness and social loneliness), such as “I experience a general sense of emptiness” and “There are plenty of people I can rely on when I have problems.” For the first three items related to emotional loneliness, answers are indicated as yes “1,” more or less “1,” and no “0.” For the last three items related to social loneliness, answers are indicated as yes “0,” more or less “1,” and no “1.”

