In recent years, the blended intervention combining face-to-face workshops and eHealth intervention anticipates that the strengths of one delivery mode would offset the weaknesses of the other (33–36). A recent meta-analysis reported that the blended intervention can significantly promote total PA levels and diet behavior among adults (37). However, whether a blended intervention is more effective than traditional face-to-face interventions is unclear. Also, only limited findings reported the effectiveness of blended interventions in promoting PA and diet among older adults.

The findings of this study aim to fill the research gap, and its research design will be outlined in the following sections. There are two research objectives in this study. The primary aim is to compare the intervention effects between blended, face-to-face, and control groups in primary outcomes, including PA, diet (FVI and MFEA), and adherence to the health recommendations of PA and diet (FVI and MFEA). The second objective is to compare the intervention effects between blended, face-to-face, and control groups in secondary outcomes, including social-cognitive variables of behavior change (i.e., self-efficacy, planning, social support, and action control), physical health outcomes (i.e., clinical indicators, senior physical fitness), mental health outcomes (i.e., depression, loneliness), and health-related quality of life (HRQoL).

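### The loneliness instruction, as printed, sends disagreement to an answer that scores as lonely on the three emotional items; the wording and the scoring need to be reconciled

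*Protocol article*

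**What the plan says.** Section 2.4.2.2 (Mental health outcomes) presents a script to be read or shown to participants. *Yes* is for statements that describe the person. The rest of the rule is: "if you disagree with the statements, answer more or less; if you do not think that they are describing you, answer no".

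The scoring follows in the same paragraph:
- Emotional items: "For the first three items related to emotional loneliness, answers are indicated as yes “1,” more or less “1,” and no “0".
- Social items: "For the last three items related to social loneliness, answers are indicated as yes “0,” more or less “1,” and no “1".

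One example item is given per domain: "I experience a general sense of emptiness” and “There are plenty of people I can rely on when I have problems". The emotional example is worded negatively and the social example positively, so the reversed scoring is coherent.

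The Introduction lists loneliness under the second objective, among the outcomes compared between the three arms: "mental health outcomes (i.e., depression, loneliness), and health-related quality of life (HRQoL". Section 2.4 fixes the timing: "All the outcomes will be measured at T1 (baseline pre-test), T2 (post-test), and T3 (follow-up". The same section says that all scales will be in Cantonese, and 2.4.2.2 says that a Chinese translation of this scale is used.

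**The concern.** The instruction separates two states that a respondent can hardly tell apart, and the scoring gives them opposite values on half the scale. Someone who disagrees that they feel empty, and follows the clause "if you disagree with the statements, answer more or less", receives the same score as someone who says yes. No clause covers a statement that is partly true, although that is what the label of the middle answer suggests.

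Because the scoring is dichotomous, the middle answer carries the full point, so a misrouted answer costs a whole point. If the printed wording is in use, it applies at all three assessments and in all three arms. The error could not be undone afterwards, because disagreement and partial agreement would share one answer code. Section 2.6 also promises participants an individual report that includes mental health outcomes after each assessment, so an inflated score could reach them.

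**Working it through.** The protocol states no figure for this scale that could be reproduced. The check has two parts: applying the printed rules to single records, and following the effect into arm differences under stated assumptions.

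**1. Single records** (scores from 2.4.2.2)

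| Respondent | Emotional answers | Emotional score | Social answers | Social score | Total |
|---|---|---|---|---|---|
| Not lonely, uses *no* for untrue statements | 3 × *no* | 0 | 3 × *yes* | 0 | 0 of 6 |
| Not lonely, follows the disagreement clause | 3 × *more or less* | 3 | 3 × *yes* | 0 | 3 of 6 |
| Lonely, uses *no* on social items | 3 × *yes* | 3 | 3 × *no* | 3 | 6 of 6 |
| Lonely, follows the disagreement clause on social items | 3 × *yes* | 3 | 3 × *more or less* | 3 | 6 of 6 |

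Misrouted disagreement adds 1 point per emotional item, at most 3. It adds nothing on the social items.

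**2. Arm differences, equal misrouting**

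Let p be the proportion who should score 1 on an emotional item, and q the fraction of the remaining answers that go to *more or less*. Neither is in the protocol; both are assumed here.

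- Observed item rate = p + (1 − p)q = q + p(1 − q).
- With the same q in both arms, observed subscale difference = 3(p₁ − p₂)(1 − q).
- The observed rate is linear in p, so with the same q at every assessment, differences in change from baseline shrink by the same factor.

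| q | Assumed rates 0.50 v 0.30 | Assumed rates 0.40 v 0.25 |
|---|---|---|
| 0 | 0.60 | 0.45 |
| 0.10 | 0.54 | – |
| 0.25 | 0.45 | 0.34 |
| 0.50 | 0.30 | 0.23 |
| 1 | 0 | 0 |

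The arm mean rises by 3(1 − p)q. For p = 0.25 it goes from 0.75 to 1.31 (q = 0.25), 1.88 (q = 0.50) and 3.0 (q = 1).

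**3. Arm differences, unequal misrouting**

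Take assumed item rates of 0.30 in arm A and 0.50 in arm B, a true difference (B − A) of 0.20.

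- q = 0.5 in A and 0.2 in B: A = 0.30 + 0.70 × 0.5 = 0.65; B = 0.50 + 0.50 × 0.2 = 0.60; observed difference −0.05.
- q = 0.2 in A and 0.5 in B: A = 0.30 + 0.70 × 0.2 = 0.44; B = 0.50 + 0.50 × 0.5 = 0.75; observed difference 0.31.

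The sign can therefore reverse or the difference can be exaggerated.

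**The case against.** The best defence is that the printed sentence is an English rendering of an instruction that participants will meet in Cantonese. A lost qualifier in translation would explain the odd middle clause, and the fielded form may be sound. This stands: the protocol cannot show which text is wrong. It does not remove the point, because the published text contradicts its own scoring and nothing elsewhere in the article corrects it.

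The second defence is that a respondent who is not lonely has a correct route in the same sentence. An untrue statement also falls under the last clause, which leads to *no* and a score of 0, and the ordering of the three labels is easy to grasp. This stands too. It makes 3 points a maximum for one respondent, not an expected error.

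A reader might infer that the wording will shrink the arm differences, push non-lonely participants to the top of the emotional subscale, or explain a null loneliness result. The protocol does not support any of these. It gives no misrouting rate and no item rates. Shrinkage follows only if misrouting is similar across arms; that is the natural expectation with one instruction for everyone, but it remains an assumption. A pile-up at the top needs q near 1, for which there is no evidence.

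The scoring rule itself is coherent and is not at fault.

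**Conclusion.** The inconsistency is real as written. Two near-identical states lead to answers scored 1 and 0 on the emotional items, and partial agreement has no clause of its own. The largest error for one respondent is +3 on the 0–3 emotional subscale and on the 0–6 total; the social items carry none. These figures follow from the printed text alone.

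The effect on the comparison between arms is not established. It is a shrinkage by (1 − q) if misrouting is equal across arms, and a bias in either direction if it is not, with q unknown anywhere between 0 and 1. Whether any participant is affected depends on the Cantonese form.

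The matter deserves correction because it is cheap to put right before data are collected and cannot be repaired from the data afterwards. Its reach is limited to half of one secondary outcome.

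**What to change.** - Compare the fielded Cantonese instruction with the scoring. Correct it if it carries the error, and correct the English text in either case. *Yes* should be for statements that describe the participant, *more or less* for statements that describe them in part, and *no* for statements that they disagree with or that do not describe them.
- Use the same wording at T1, T2 and T3.
- If any assessment has already used the printed wording, keep the stated scoring as the main analysis and add one sensitivity analysis that scores *more or less* as 0 on the three emotional items. Present it as a bound, not a correction, because it misclassifies respondents who truly agree in part. The two scorings bracket the arm difference only if true partial agreement makes up the same share of *more or less* answers in each arm; state that with the result.

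The cost is one sentence in the questionnaire and in the article and, if data already exist under the printed wording, one extra analysis. No additional participants or procedures are needed.

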##### Social-cognitive factors

2.4.2.3

The validated questionnaires will be used to assess the four social-cognitive variables (56–58), including Questionnaires of Self-efficacy (five items for each behavior) (59), Questionnaires of Planning (six items for PA, four items for each diet behavior) (60, 61), Questionnaires of Social Support (3 items for each behavior) (62), and Questionnaires of Action Control (6 items for each behavior) (63).

##### Health-related quality of life (HRQoL)

2.4.2.4

A brief version of the World Health Organization’s Quality of Life questionnaire (WHOQOL-BREF HK) will be used to evaluate the HRQoL (62) in Hong Kong. Participants will be first asked about their general quality of life using the question “How would you rate your quality of life?” on a two-item five-point scale (1 = very poor; 5 = very good). The physical health subdomain with seven items will also be used (Cronbach’s *α* = 0.71), such as “Are you satisfied with your ability to do everyday things?” and “Do you have enough energy to cope with daily life?” (1 = very dissatisfied; 5 = very satisfied). However, for item 3 and item 4, the participants will be asked, “Do you need medical help to cope with everyday life?” and “Do you feel pain and discomfort holding you back?” (1 = an extreme amount; 5 = not at all).

##### Demographics

2.4.2.5

Items will include name, mobile number, gender, age, marital status, number of children, educational level, professional status, household income, and history of chronic diseases.

### Pilot study

2.5

A pilot study of blended intervention was run before the main study. The aim was to ensure that the recruitment procedure, data collection instruments, and intervention content were feasible and acceptable. The preparation study was conducted for 4 weeks. Four older adults were recruited through Purposive Sampling with two females and two males (Mean age = 69.3 years, SD = 3.30) (64).

The participants were asked to finish all the measurements once and to attend a 4-week blended intervention program. The intervention content was the same as the first 4-week out of the proposed 10-week intervention content in the main study. After finishing the pilot study, the participants were invited to give suggestions and feedback. Depending on the input from the participants (e.g., making web pages more accessible to operate, shortening the health talk), the intervention content was further adapted. The participants in the pilot study will not be involved in the main study.

### Retention strategies

2.6

Different strategies will be applied to improve the adherence rate of the three assessments and the participation rate of all intervention sessions throughout the program. Such methods will include (1) a WhatsApp message will be sent to older adults in all groups 1 day before the interventions start to remind participants to participate by then; (2) there will be a check-in before each face-to-face class to help participants and researchers keep track of the attendance rate of all study participants throughout the course; (3) the printed materials of the face-to-face health talk will be distributed to the older adults in each face-to-face session. Since older people tend to have declining memories, this will help them look it up at home after they finish the course; (4) starting from the fifth week, the participants who document a valid diary three times a week on the website for each behavior will receive a cash reward of $10HKD, which will be distributed once a week; (5) after the completion of each data collection (T1, T2, and T3), the individualized health report including physical and mental health outcomes will be provided to the older adults.

### Data analysis

2.7

All data will be analyzed by using SPSS 29.0. The Expectation Maximization (EM) method will be applied for missing values. Intention-to-treat principles will be used for all analyses. Independent samples *t*-tests, *F*-tests, and Chi-square tests will be used to compare the baseline characteristics at T1. Statistical significance will be set at the 5% level (two-tailed).

A series of generalized linear mixed models (GLMM) will be applied to evaluate the intervention effects on behaviors (PA, FVI, and MFEA), social-cognitive variables of behaviors (i.e., self-efficacy, planning, social support, and action control), physical health outcomes (i.e., physical fitness test, clinical indicators), mental health outcomes (i.e., depression, loneliness), and health-related quality of life (HRQoL).

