### Target population

2.2

Participants will be recruited from two Senior Centers in Hong Kong. The e-poster and video will be advertised by the staff in the Senior Centers. There are over 3,000 members in these two centers. Therefore, recruiting participants by advocating for the Senior Centers is feasible and advantageous. Potential study participants will be informed that there will be a health promotion program in which they can obtain health-related programs and receive a $300HKD (about $39USD) supermarket gift card as an incentive if the participants complete the 10-week health project and finish three times data collection.

Once the older adults express their interests, they will be encouraged to register in the program. After finishing all the registration and eligible screening, they will receive the study consent forms. The eligible criteria include: (1) aged 65 years and above; (2) owning a smartphone and having access to the Internet; (3) passing the Physical Activity Readiness Questionnaire (PAR-Q); (4) having sufficient reading and listening skills in Cantonese; (5) at least one health behavior (PA, FVI, MFEA) fails to meet the recommended health guideline. Exclusion criteria will include: (1) under special situations that seriously affected their diet (e.g., oral allergy syndrome) and mobility (e.g., physical disability); (2) meet all the health guidelines of PA, FVI, and MFEA; (3) participate in other ongoing project related to PA and diet intervention. Then, all participants will be allocated to one of three groups with an equal ratio (in a 1:1:1 ratio). The group allocation will be blinded. The researchers will provide the individual web link for the blended intervention group participants.

The sample size was calculated using G*Power 3.1 software. For achieving a medium effect size (Cohen’s *f* 0.26) on PA and diet based on a previous similar blended study among adults (35), with a statistical power (1-*β*) of 0.8 and an alpha of 0.05 (38), a total of 91 participants is required for the three groups (IG-1, IG-2, and CG). Considering the dropout rate of approximately 20% (35), a total of *N* = 114 participants is required to enable a robust evaluation.

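### A single EM fill followed by a mixed model that reads the filled values as data either breaks the 5% level or shrinks the effects at the planned 20% dropout

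*Protocol article*

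**What the plan says.** Section 2.7 (Data analysis) of the protocol article names the software, "All data will be analyzed by using SPSS 29.0", and gives one rule for incomplete data: "The Expectation Maximization (EM) method will be applied for missing values". It continues with "Intention-to-treat principles will be used for all analyses" and "Statistical significance will be set at the 5% level (two-tailed"). Effects are then tested by mixed models: "A series of generalized linear mixed models (GLMM) will be applied to evaluate the intervention effects on behaviors (PA, FVI, and MFEA"). The same sentence extends this to the social-cognitive, physical, mental-health and quality-of-life outcomes. Section 2.4 has outcomes measured at T1 (baseline), T2 (post-test) and T3 (3-month follow-up).

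Section 2.2 (Target population) gives the expected loss, "Considering the dropout rate of approximately 20" per cent, and moves from 91 to 114 participants on that account.

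The article names no multiple imputation, no random residual added to filled values, no standard-error correction and no sensitivity analysis. It does not say whether arm enters the EM model.

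**The concern.** EM estimates a mean vector and a covariance matrix. When it is used to complete a data file, each missing value becomes its conditional expectation given that person's other values, with no residual noise. A model fitted to that file cannot tell a prediction from a measurement.

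Two different harms can follow:

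- **Arm in the EM model.** Filled values lie exactly on the fitted line of their own arm. Residual variance is understated and the sample size overstated, so p-values are too small.
- **Arm not in the EM model.** A dropout's filled values are predicted from the pooled data and carry no arm difference. The estimated effect moves towards zero.

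All the primary behaviour outcomes pass through this step. In the first case a claim that the blended arm is superior could be spurious at well above the stated 5%. In the second, a trial sized for 80% power loses some of it and reports a diluted effect.

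**Working it through.** **Inputs from the article.** Three arms, 1:1:1; 91 evaluable and 114 randomised; 20% dropout; three visits; "For achieving a medium effect size (Cohen’s *f* 0.26) on PA and diet", "with a statistical power (1-*β*) of 0.8 and an alpha of 0.05"; two-sided tests.

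**Assumptions not in the article.** One conditional-mean fill; the mixed model run on the filled file; normal outcomes; values missing completely at random; correlation between visits (ρ) of 0.3 to 0.7. Effects are 0.50 SD for the T2 contrast. For the three-visit model they are 0.60 SD (blended) and 0.30 SD (face-to-face).

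**1. The plan's own figure.** For a group-by-time test with 3 groups and 3 times, λ = f²·N·(m−1) = 0.26² × 91 × 2 = 12.30, with 4 and 2(91−3) = 176 degrees of freedom. Power is 0.8015, so 91 reproduces. Then 91/0.80 = 113.75, rounded up to 114, or 38 per arm. The sample size is not in error. It treats dropouts as lost information, whereas the filled analysis would claim information from all 114.

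**2. Closed form, arm in the EM model.** With a fraction d missing, residual variance is multiplied by about (1−d), and n is overstated by 1/(1−d):

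reported SE / true SE ≈ √[(1−d)·(1−d)] = 1−d

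- d = 0.20: actual level = 2[1−Φ(1.96 × 0.80)] = 2[1−Φ(1.568)] = 11.7%.
- d = 0.10: 2[1−Φ(1.764)] = 7.8%.

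**3. Closed form, arm not in the EM model.** If T2 and T3 are both missing, the expected effect is (1−d)·δ + d·0. For d = 0.20, 0.50 becomes 0.40 and 0.60 becomes 0.48.

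**4. Simulation, baseline-adjusted contrast at T2, 38 per arm, 20% missing.** At ρ = 0.5 with arm in EM, the true SD of the estimate is 0.220 and the mean reported SE is 0.177 (ratio 0.80), with type I error 11.7%. A repeat over ρ 0.3 to 0.7 gave 11.7% to 12.3%. Without arm, 0.50 is estimated as 0.40. Observed data only: 4.5% to 5.0%, no bias. With 10% missing at T2: 7.2% to 8.1%, or an estimate of 0.45.

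**5. Simulation, three-visit random-intercept model, group-by-time test, 3,000 replicates per setting, 20% missing at T2 and T3.**

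| ρ | Type I, EM with arm | Type I, EM without arm | Type I, observed data | Power, EM without arm | Power, observed data |
|---|---|---|---|---|---|
| 0.3 | 0.157 | 0.055 | 0.056 | 0.383 | 0.445 |
| 0.5 | 0.174 | 0.055 | 0.054 | 0.515 | 0.579 |
| 0.7 | 0.178 | 0.048 | 0.047 | 0.777 | 0.818 |

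With arm in EM the effect is unbiased (0.60) but the model SE is 0.83 to 0.86 of the true SE. Without arm, 0.60 is estimated as 0.48. Observed data give 0.60 and an SE ratio of 0.99 to 1.02.

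The level is worse here than in step 4 because four contrasts are tested jointly. With an SE ratio of 0.83, the χ² cut-off of 9.49 on 4 df is in effect 9.49 × 0.83² = 6.54. The exceedance probability is e^(−3.27) × (1 + 3.27) ≈ 0.16, close to the simulated values.

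**6. Other dropout patterns, ρ = 0.5.**

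| Missing T2 / T3 | Type I, EM with arm | Estimate of 0.60 at T2, EM without arm | Type I, observed data |
|---|---|---|---|
| 5% / 10% | 0.083 | 0.57 | 0.050 |
| 10% / 20% | 0.118 | 0.54 | 0.050 |
| 20% / 20% | 0.174 | 0.48 | 0.054 |
| 30% / 30% | 0.269 | 0.42 | 0.053 |

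For 10% / 20%, the range with arm over ρ 0.3 to 0.7 is 0.118 to 0.147.

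**The case against.** The article never says in words that the mixed model runs on an EM-completed file. The trial uses several multi-item scales, so EM could be meant only for skipped items. Whether arm enters EM is the kind of detail a condensed article may leave to a fuller plan. The two harms are alternatives and differ in gravity: without arm the level stays near 5%, and the power loss is about 4 to 6 percentage points. The 20% in section 2.2 is an overall allowance; if losses build up, fewer than 20% are missing at T2 and the harm there is smaller.

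Some of this stands. The size of the harm depends on the dropout pattern and on an unstated setting, so a range is the right way to report it. One further worry, that EM assumes normality and so gives fractional or out-of-range values for GDS-15, loneliness and guideline adherence, was not simulated. For adherence it arises only if EM is run on the yes/no indicator itself, not on the minutes, portions or taels behind it. The conclusion does not rely on it.

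The rest does not rescue the rule. The item-only reading is strained beside intention-to-treat for all analyses and a planned 20% loss. The article also states a method here; it has not merely left one out. Neither setting of the EM model gives a sound analysis: one fails on the level, the other on the estimate. Even at 5% / 10% missing, the level with arm is 8.3%.

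**Conclusion.** The rule is wrong as written and must be fixed before analysis. At 20% missing and with arm in EM, the nominal 5% becomes about 12% for a baseline-adjusted T2 contrast and 16% to 18% for the three-visit group-by-time test. With arm left out, effects shrink by about the dropout fraction (20%) and power falls. With 10% missing at T2 and 20% at T3, the three-visit level is 12% to 15%, or the T2 effect shrinks by about 10%. The same mixed model without filling has neither fault under these conditions.

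The direction within each branch is secure. The sizes rest on the assumptions listed with the calculations, chiefly a noise-free single fill, normal outcomes and data missing completely at random.

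**What to change.** Delete the EM sentence in section 2.7 and state instead:

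- The mixed models are fitted by maximum or restricted maximum likelihood to all observed T1, T2 and T3 records of all randomised participants in their allocated arm. Missing outcomes are not filled in beforehand. This is valid if data are missing at random given what the model contains, and a participant with only a T1 record stays in the analysis.
- As a sensitivity analysis, multiple imputation with arm, baseline and all visits in the imputation model, combined by Rubin's rules. A further analysis for data not missing at random would be a useful addition.
- If EM was meant only for skipped items within a scale, say so and restrict it to that.

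The cost is a few sentences, with no extra data or participants. Compared with EM including arm, reported standard errors rise to their honest size (in the T2 example from 0.177 to about 0.220, or 0.220/0.177 = 1.24 times). The target of 114 can stay, since it already allows for the lost information.
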